# Scientific rigor

If the results indicate the existence of a clinically significant effect of IMS, then a larger study with greater attention to mechanisms would be indicated in future. By including both control groups (exercise alone, sham needling), the study design will allow appropriate conclusions to be drawn. If an exercise alone group is not included and if the sham needling and IMS groups were equivalent, then we would not know if IMS and sham needling are equally effective or equally ineffective. Conversely, if we did not have a sham needling group and if the IMS group were superior to exercise group, then we could not conclude that IMS is effective – the effects may have been due to a non-specific effect of needling.^63^ After 50% of the patients, have been enrolled, one researcher (AS) will check the patient baseline data to ensure that the randomized groups are equivalent (in terms of symptom duration, gender, age, baseline VISA-A). If necessary, the subsequent randomization will be weighted in consultation with UBC statistical consulting services. The RCT will be reported and conducted according to the guidelines of the CONSORT (CONsolidated Standards Of Reporting Trials) statement 2010, and ensuring that a score of 10/11 is achieved on the PEDro score (physiotherapy evidence database). It is not possible to blind the treating therapist therefore a score of 11/11 is not possible.

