# Study Design

This is a prospective, single blind, randomized controlled trial with three groups. All groups will receive standard 12 week physiotherapy program provided by LS, including a standardized and progressive eccentric training and strengthening program. The first group will receive IMS (detailed below), while the second will receive an equivalent number of sham (superficial non-intramuscular) needling sessions. The third receives the progressive exercise training program alone. Patients will be recruited from the clinical practice of LS and colleagues; additionally, the study will be advertised through LS’s and AS’s contacts in the IMS, UBC, Physiotherapy Association of BC, and Vancouver Coastal Health networks. After providing informed consent and being screened for inclusion/exclusion criteria, diagnosis will be confirmed by physical examination. Inclusion criteria include subjects 19 to 60 years of age, fluent in English, with a 3 month minimum symptom duration, evidence of midportion Achilles tendinopathy on physical examination and tendinosis on ultrasound; and objective signs by Gunn IMS assessment of neuropathic change in the L5-S2 segmental levels including the presence of taut muscle bands amenable to IMS.^49^ Tight bands palpated in muscles paraspinally (dorsal rami) from T1 down and peripherally (ventral rami) from T12 down will also be treated in the IMS group, but participants without findings in the L5-S2 levels will be excluded to limit variability among subjects. Exclusion criteria include IMS contraindications (infection in the area, pregnancy, bleeding disorders, history of bacterial endocarditis, post-surgical implant in last four to six months and major surgery in the last three months), previous treatment with IMS or TCMA (for blinding purposes); true leg length difference of greater than ½” previous corticosteroid injections or recent fluoroquinolone use and systemic inflammatory disease. Those demonstrating the presence of other syndromes that cause pain in and around the Achilles tendon will be excluded by history-taking and physical examination: partial tearing, posterior ankle impingement/ os trigonum syndrome, tenosynovitis, dislocation of the peroneal or other plantar flexor tendons, irritation or neuroma of the sural nerve or insertional Achilles pain. Patients will be randomized by the research assistant ([name]) who is blinded to the patient’s baseline data using a random number generator (SPSS v.16.0).

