## Study Team and Roles

**[name]**

Conduct initial phone screen (with [name] and [name]).

After final eligibility screen by [name] and informed consent obtained, consult random number generation table and record subject group allocation, ensure confidentiality of files (must be in a locked cabinet accessible only by the study team).

Collate initial subject files and deliver to locked cabinet at Kinetic clinic.

Prepare patient exercise diary with appropriate dates filled in.

Collect hard copies of data (VISA-A forms and Global Improvement forms completed by study participants, ankle ROM forms completed by MB, treatment attendance data logged by LS) from locked cabinet at Kinetic and enter into Master Tracking Sheet on password-protected computer.

Monitor patient flow through study, ensure all appointments are booked and confirmed when they happen, including assessment by MB and UTC scans by LS, as per Master Tracking Sheet.

Maintain unblinding log.

Contact participants re 1 year follow-ups.

Send de-identified data (e.g. copies of Master Tracking Sheet) to [name] or designate upon request.

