# Statistical analysis

Based on the published literature, we estimate that the no-needling and sham needling groups will improve on average by 20 VISA-A points after 12 weeks (due to the effects of exercise-based physiotherapy management),^25^ and we hypothesize that the IMS group will improve by a further 15 points (the minimum clinically significant difference).^42^ The SD of a single VISA-A score is 15^67^, and correlation between repeated measurements on the same patient after 1 week is 0.80.^67^ This makes the SD for the difference between 2 measurements on the same patient approximately 9.5. To detect these effects in a one-way ANOVA model with a residual standard deviation of 9.5 with power 95%, a sample size of 11 patients is needed in each group for a total of 33 patients. Assuming a 20% drop-out rate,^43^ 42 patients will initially be recruited and enrolled. The primary analysis will be a one-way Analysis of Variance with the response being the change in patients VISA-A score at 12 weeks. Secondary analyses will be performed on the change in patients VISA-A score at 6 months and 12 months from baseline, and on changes in dorsiflexion range of motion and global improvement scale. Inter-group post-hoc tests will be conducted in consultation with UBC statistical consulting services ([name], manager). Intention to treat analysis will be employed. If a clinically significant effect of IMS in Achilles tendinopathy exists, this pilot study has a 95% chance of successfully detecting it. If there is no clinically significant effect of IMS in Achilles tendinopathy, this study has a 95% chance of reaching this conclusion.

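### The protocol states no restriction on randomisation and allows an undefined, threshold-free change of allocation at the midpoint after one researcher compares the groups

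*Protocol*

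**What the plan says.** Under Study Design the trial is a "single blind, randomized controlled trial with three groups", and the research assistant, who does not see baseline data, allocates patients "using a random number generator (SPSS v.16.0". Under Study Team and Roles the assistant's task, after eligibility and consent, is to "consult random number generation table and record subject group allocation". The text names no blocks, strata, minimisation or ratio. Equal groups are implied only by the sample size sentence.

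Scientific rigor adds a midpoint step: "After 50% of the patients, have been enrolled, one researcher (AS) will check the patient baseline data". The aim is "to ensure that the randomized groups are equivalent (in terms of symptom duration, gender, age, baseline VISA-A". The consequence is conditional: "If necessary, the subsequent randomization will be weighted in consultation with UBC statistical consulting services".

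Under Statistical analysis the primary test is a one-way ANOVA of the 12-week change in VISA-A. It names no baseline covariate and no term for the phase of randomisation.

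**The concern.** Under sound randomisation any baseline difference between arms is due to chance. A check meant to ensure equivalence at about 7 per arm will therefore often report a difference when nothing has gone wrong. The protocol does not say how large a difference triggers action, what the action is, or whether the researcher sees which arm is which. The allocation rule for the second half then depends on a judgement made with group summaries in view, and nobody can later reconstruct what would have been done had the groups looked different.

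Two things are at stake. The step may not achieve its purpose, and it may move arm sizes away from the equal groups that the power calculation assumes. Meanwhile the primary analysis does not use the simplest protection against baseline imbalance, which is adjustment for it. Detail left to a separate analysis plan would not be a finding. Here the protocol itself fixes a mid-trial change of allocation and fixes it badly.

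**Working it through.** **1. The plan's own figures (Statistical analysis).** Inputs: SD of one VISA-A score 15, correlation 0.80, mean changes 20, 20 and 35, drop-out 20%. Alpha is not stated for the power calculation; 0.05 is assumed.
- SD of change = 15 × √(2 × (1 − 0.80)) = 9.49 (protocol: 9.5).
- Noncentrality at 11 per arm = 11 × (5² + 5² + 10²) / 9.5² = 18.3. The noncentral F with 2 and 30 degrees of freedom gives power 96.2%. At 10 per arm power is 94.1%, so 11 is the smallest size that reaches 95%.
- 33 / 0.8 = 41.25, taken to 42 for three equal arms.

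All three reproduce.

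**2. What chance produces at the midpoint.** Half of 42 is 21, or about 7 per arm. Covariates are taken as independent and normal.
- Standard error of one arm's mean VISA-A = 15 / √7 = 5.7 points.
- Simulated span between the highest and lowest of three arm means: median 9.0 points, above 10 points in 42% of trials.
- At least one of the three continuous factors (symptom duration, age, VISA-A) spans more than 0.8 SD in 65% and more than 1 SD in 38%.
- If the check were four independent tests at 5%, at least one would be significant by chance in 1 − 0.95⁴ = 18.5%.

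At the full 14 per arm the VISA-A span falls to a median of 6.4 points, above 10 points in 18%. The midpoint figures show how easily the check is set off, not how unbalanced the final trial would be.

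**3. Whether weighting repairs it.** One continuous covariate was simulated, keeping trials whose midpoint spread was at least 0.8 SD (mean about 1.06 SD).

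| Second-half allocation | Final spread |
|---|---|
| Equal, 7/7/7 | 0.59 SD |
| Arm-level weighting: 9 to the most deviant arm, 6 to each other arm | 0.57 SD |
| Covariate-adaptive, preferred arm with probability 0.8 | 0.20 SD |

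Arm-level weighting does little because new patients have the same expected covariates whichever arm they enter. An initial 10-point deviation in 7 patients is diluted to 10 × 7/14 = 5.0 points by 7 more patients and to 10 × 7/16 = 4.4 points by 9 more.

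**4. Arm sizes under unrestricted 1:1:1 allocation.** At 21 enrolled, some arm has 4 or fewer patients in 36% of trials. At 42, some arm has 10 or fewer before any drop-out in 37%. With each patient then dropping out with probability 20%, average power stays near 95% and is below 90% in about 9% of trials. A completer split of 13/13/7 with the IMS arm smallest gives 89%.

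**5. What reaches the primary result.** With equal SDs at both times, a baseline gap D leaves (1 − ρ) × D in the difference in mean change.
- ρ = 0.80 (protocol, measured over 1 week): 0.20 × 10 = 2 points.
- ρ = 0.50 (assumed for 12 weeks): 0.50 × 10 = 5 points.

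The hypothesised difference is 15 points: "we hypothesize that the IMS group will improve by a further 15 points".

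**The case against.** The strongest reply is that the step is conditional, requires statistical advice and looks only at baseline data. That stands as far as it goes. The protocol does not commit to re-weighting, and consultation is a safeguard, but consultation after the data are seen is not a prespecified rule.

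Four stronger readings are tempting and are not supported.

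- *The weighting cannot repair the imbalance.* This holds only if arm probabilities are altered. The protocol leaves the form open, and covariate-adaptive assignment would cut the spread substantially. That reading sits awkwardly with allocation from a table by someone who does not see baseline data, so those passages would have to change, but it is not excluded.
- *The check is unblinded, or driven by outcomes.* The protocol says neither that labels are visible nor that they are masked. Statistical services are also to analyse data at the midpoint of recruitment, with no scope given, but nothing links that analysis to the allocation step.
- *The trial becomes underpowered.* Average power stays near 95% even under simple randomisation. How the table was built is not described, so simple randomisation is itself an assumption.
- *The baseline imbalance passes into the result in full.* For VISA-A it does not, because the change score removes most of it at the stated correlation. The change score does not by itself adjust for the other three factors.

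**Conclusion.** The point holds as a defect of a rule that the protocol fixes: no stated restriction at the start, followed by a discretionary mid-trial change with no threshold, no definition and no statement on masking. Chance alone would often invite its use (42% of trials for a VISA-A span above 10 points; 38% for a span above 1 SD on at least one of the three continuous factors). On the reading that best fits the described process it would gain almost nothing.

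The likely damage to the primary comparison is modest: about 2 points from a 10-point baseline gap at correlation 0.80, about 5 points at an assumed 0.50, and power below 90% in roughly one trial in eleven. These sizes rest on equal intended allocation, independent normal covariates, equal SDs at both visits and alpha 0.05. The change is worth making because it is cheap and removes an avoidable question about how patients were allocated.

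**What to change.** 1. Delete the midpoint re-weighting from Scientific rigor. A descriptive baseline table at the end of the trial is enough.
2. From the first patient, use either permuted blocks of varying size or minimisation with a random element that includes baseline VISA-A, prepared by UBC statistical services. State the 1:1:1 ratio. Varying block sizes matter because the practitioner who screens patients also treats them and so sees past allocations. Blocks keep the arm sizes close but do not balance covariates; the ANCOVA in item 3 deals with baseline VISA-A. Minimisation would also require revising the text under Study Design and Study Team and Roles, because it needs each patient's baseline values at allocation.
3. Replace the one-way ANOVA of change by an ANCOVA of the 12-week VISA-A score with baseline VISA-A, and any balancing factor used, as covariates.

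If recruitment has begun, leave the existing list alone, drop the re-weighting and make only the ANCOVA change.

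Cost: minor set-up work by a statistical group already involved, and one or two degrees of freedom in the primary model.

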# Ability to do the work

[name] is an experienced IMS practitioner. [name] has fourteen years of experience working as a physiotherapist and holds a Bachelor of Applied Science in Physiotherapy and a Master of Manual Therapy, has certification in Gunn IMS and is a member of iSTOP. Given the prevalence of Achilles tendinopathy and the offer of free physical therapy treatment, recruitment will not pose any threat to the success of this study. [name] is an Assistant Professor in Physical Therapy with protected time for clinical research (Michael Smith Scholar award) with postgraduate AFCI training (Acupuncture Foundation of Canada Institute). Not only are we ideally placed to conduct this project in clinical and research skills, we are very well networked with professional organizations and as such the results can be immediately disseminated to target groups including iSTOP members (please see letter of support fom iSTOP education director), UBC MPT students, PABC members, the national and international physiotherapy communities (Canadian Physiotherapy Association and International Federation of Orthopaedic and Manipulative Physiotherapists), Worksafe BC healthcare providers, as well as other research interest groups (e.g. Instititute of Musculoskeletal Health and Arthritis). [name] is a member of the PABC-UBC Tendinopathy Task force which develops and distributes clinical resource materials to B.C. clinicians. Please see [name] CV for other details of knowledge translation work.

**Limitations**

This is a relatively small clinical trial (target starting population, n=42). However, we note that this population is consistent with other recent clinical trials in high impact Sports Medicine journals for midportion AT (e.g. Yelland et al, 3-arm trial, similar design to ours, starting n=43^42^). Our sample size was arrived at via power calculation conducted by UBC statistical services. Although the study is powered to detect clinically significant differences between treatment groups, its generalizability may be limited by the treatment population (recreational athletes with tendinosis on US and with L5-S2 region-specific signs identified by an IMS assessment). If the trial demonstrates a clinical effect of IMS on chronic midportion AT in these patients, further study with other populations (e.g. elite athletes or workers) would be indicated. Additionally, the inter- and intra-observer reliability of the IMS assessment procedure has not been documented to our knowledge; in this case, a single experienced IMS practitioner will conduct the assessments. A further limitation is that it is not possible to create a truly sham IMS treatment, as the technique creates a strong, distinctive sensation. Our compromise is to use sham superficial (skin) needling to control for at least a portion of the expected placebo response, however there are no published data on the magnitude of placebo response to needling for AT. A further limitation is that the groups which receive needling (sham or IMS) vs exercise alone have slightly different visit numbers, and that the number of exercise sessions will be slightly fewer for the needling groups (they are typically asked to refrain from exercise for 24 to 48 hours after needling sessions). However, the magnitude of these differences is not enough to cause a meaningful clinical difference in our experience.

**Significance**

This study will be the first iSTOP-UBC collaborative study and the first RCT examining the effect of IMS on AT, the vast majority of which are associated with taut muscle bands that are highly amenable to IMS. If successful, this study would be likely to stimulate further research by ourselves or other groups, e.g. examining the effects of IMS on other tendinopathies such as the lateral elbow. [name] has argued convincingly that the rationale for IMS in chronic tendinopathies involves the ability to relieve associated muscle shortening, (e.g. ^49^ p 265,266) but this hypothesis has not yet been tested by a blinded assessor as we propose to do here. The prevalence of AT is high and its impact on physical activity is significant, with up to 20% of patients experiencing pain and activity limitation after 5 years despite optimal management^48^. This proposal addresses a recognized gap between clinical experience and research evidence, and the results will thus be directly relevant and of potentially high impact to practising clinicians and their patients.

